## Abstract

**Background:**

In Nigeria, breast cancer incidence is rising, late presentation is common, and outcomes are poor. Patient-related factors such as lack of awareness and misperceptions in addition to health system deficiencies such as lack of a clearly defined framework for breast cancer screening and referral are some of the major drivers of this poor outlook. Guidelines for breast cancer screening in high-income countries have limited applicability in low-middle-income countries, hence the need for innovative, resource-compatible strategies to combat the negative trend. This manuscript presents our study protocol which aims to evaluate the impact of a novel breast cancer early detection program developed to address delayed presentation and lack of access to diagnostic and treatment facilities in South-West Nigeria. This entails the use of mobile technology (innovative handheld iBreast Exam [iBE] device, mobile breast ultrasound, and mobile mammography) and patient navigation as interventions at the community level.

**Methods:**

The study (ClinicalTrials.gov identifier: NCT05321823) will adopt a randomized two group clinical trial design with one local government area (LGA) serving as an intervention arm and another serving as the control. Both LGAs will receive breast cancer awareness education but only one will receive the interventions. In the intervention arm, asymptomatic (40–70 years) and symptomatic (30–70 years) women will be invited for breast evaluation which will be performed by trained Community Health Nurses using Clinical Breast Exam (CBE), and iBE. Those with positive findings will proceed to imaging using mobile mammography and ultrasound brought to the LGA every month. Symptomatic women with negative findings on CBE and iBE will be scheduled for repeat clinical evaluation on a short-term basis (one month). The Radiologist will obtain core needle biopsies as indicated and transfer them for prompt pathological assessment. Women presenting to the Primary Healthcare Centers in the control LGA will be referred directly to Obafemi Awolowo University Teaching Hospitals Complex as per the current standard of care. Records of all breast cancer cases seen in the two LGAs during the study period will be obtained. The program metrics will include screening participation rate, cancer detection rate, stage at diagnosis, and timeline from detection to initiation of treatment. The stage at diagnosis and timeline from detection to treatment compared between the two LGAs will be used to assess the impact of the intervention. The study is proposed for 2 years; however, a descriptive analysis will be carried out at 1.5 years to evaluate the retention of the study participants.

**Study significance:**

It is anticipated that this study will provide vital data to support wider breast cancer screening efforts in Nigeria.

## Introduction

Breast cancer is a major public health challenge in Nigeria with an incidence of 52/100,000 [1], three-fold higher than the incidence four decades ago. Breast cancer incidence is projected to continue to increase in the coming decades. More worrisome, however, is the pattern of presentation–up to 80% of breast cancer cases in Nigeria present in advanced stages [2, 3]. This contributes significantly to high breast cancer mortality rates. This pattern of late presentation has remained unchanged over the last three to four decades [4]. Consequently, when combined with limited access to treatment overall, breast cancer survival in Nigeria is poor compared to high-income countries (HICs) [5–7]. Given the projected rise in breast cancer incidence, there may be an epidemic of advanced breast cancer cases without effective intervention in the coming years [8]. In addition to some recognized biological factors accounting for aggressiveness, it is clear that correctible epidemiological and system-related factors play major roles in late-stage presentation [9]. Both patient and system-related factors contribute significantly to delayed presentation [10]. Delayed presentation and lack of access to diagnostic and treatment facilities are recognized principal factors accounting for poor outcomes in low-middle-income countries (LMICs) [11, 12]. Patient-related factors include lack of breast cancer knowledge, fear of a cancer diagnosis and treatment, use of traditional and alternative remedies, and financial constraints. Awareness creation, community education, and advocacy to address erroneous patient beliefs must therefore form the basis of any early detection program. In addition, a lack of accessible breast cancer screening and the absence of a clearly defined clinical pathway for evaluating women with breast masses, coupled with limited access to diagnostic and treatment facilities, are key system factors requiring intervention [13].

Currently, there are no local data to support a specific breast cancer screening model in Nigeria. Developing a successful breast cancer screening program in a resource-limited setting requires substantial logistical and cultural considerations. Although mammography is recommended as the gold standard based on data from HICs, there are personnel, financial, and infrastructural challenges that limit its applicability for routine use in Nigeria [14].

This underscores the need for a cost-effective screening model tailored to the available human and infrastructural capabilities and designed to meet individual patient needs.

Various guidelines, such as the Breast Health Initiative Resource Stratified guidelines, have been proposed for context-appropriate breast cancer screening in resource-limited settings [15]. This includes the role of primary health care workers in performing CBE, creating awareness, and patient navigation for prompt treatment. Drawing from experiences of countries that have successfully demonstrated the feasibility of breast cancer screening performed by community workers using less expensive modalities, such as CBE, it is logical to build on such models [16–18].

The iBreast Exam (iBE) (UE Life Sciences, Philadelphia, PA) is a 510(k) FDA-cleared device that utilizes sensors to electronically palpate the breast when pressed against the skin. It can be used with minimal training. It does not distinguish malignant versus benign findings but identifies women who should undergo additional evaluation for a possible abnormality. This could be particularly useful in low-resource settings with limited breast imaging available [19].

A previous study in our population has shown that the combination of the iBE device with CBE has higher sensitivity for detecting suspicious breast lesions when compared to CBE alone (92%, 95% CI 77–98 vs 83%, 95% CI 67–94 respectively) [19]. This research builds on our previous results and findings of a study utilizing iBE in India [20]. This study proposes an early detection model that combines iBE with CBE to reduce the subjectivity of CBE, as the basic breast cancer screening tools for eligible women in the community and breast imaging (mobile mammography and ultrasound) for selected women based on clinical history, CBE, and iBE findings. The components of the triple mobile assessment in this proposed project are nurse breast exams (with iBE and CBE), mobile portable ultrasound, and mobile mammography.

This manuscript aims to describe the protocol for screening women between 40 and 70 years and diagnostic evaluation of women aged 30–70 years with breast symptoms in the first comprehensive community-based breast cancer program that offers screening, and diagnostic evaluation and provides a referral pathway and patient navigation for breast cancer treatment in Nigeria.

We hypothesize that this study will increase breast cancer screening participation rates, facilitate increased uptake of breast evaluation in communities with poor geographical access to standard breast imaging, reduce the incidence of advanced breast cancer cases, and shorten patients’ timelines from presentation to diagnosis and initiation of treatment.

## Materials and methods

### Aims

The goal of this study is to establish a novel community-based breast cancer program to address delayed presentation and lack of access to diagnostic and treatment facilities in South-West Nigeria. This study aims to develop a routine community-based breast cancer screening/evaluation program incorporating awareness creation, iBE device, CBE, mobile mammography, and portable ultrasound in a selected intervention LGA; to create a referral pathway from the community to the tertiary hospital for women with positive findings in the intervention LGA; and evaluate the impact of this proposed program on the cancer detection rate (CDR), stage at diagnosis and treatment timelines in the intervention LGA compared to a non-intervention control LGA.

### Study design and setting

This project will be carried out in Osun State, Nigeria. Osun State, located in southwest Nigeria, comprises thirty Local Government Areas (LGAs). The study will use a randomized two group clinical trial design with one LGA serving as the intervention arm (Ife North LGA) and another LGA serving as the control arm (Ife East LGA). The two LGAs are located within the same state and consist of a homogenous group of people with similar demographics, culture, language, belief system and occupational pattern. Both Ife North and Ife East LGAs are made up of 10 wards each with an estimated population of 153,694 and 188,087 respectively based on the 2006 National census. This was projected to be 188,000 and 231,000 respectively in the year 2020 using annual population change of 1.6% for Nigeria between 2006 and 2022 [21]. The population projection assumes the same rate of growth for all LGAs within a state. Each ward is served by a dedicated primary healthcare centre (PHC). The two LGAs are similar in that they are in the same State with similar sociocultural characteristics and are within the catchment area of the Obafemi Awolowo University Teaching Hospitals Complex (OAUTHC), which is the referral centre for the two LGAs. Both LGAs will receive awareness and education, but only the intervention LGA will receive community-based breast evaluation and navigation. However, the control LGA located at coordinates; latitudes 7° 31′ N and 7° 34′ N and longitudes 4° 30′ E and 4° 34′ E has adequate access to screening and diagnostic evaluation because it is about 4 kilometers to the OAUTHC where radiological (including ultrasound, mammography, computerized tomography, and magnetic resonance imaging services), pathological and surgical specialty services for breast cancer screening and management are available. The intervention LGA located at coordinates; latitude 6° 58′ and 7° 35′ N and longitude 4° 22′ and 4° 37′ E is about 25 kilometers form OAUTHC. The referral center (OAUTHC) is in Ife central LGA and falls within the latitude 07° 30^′^ 0.0^″^ to 07° 31^′^ 6.71^″^ and within longitude 4° 33^′^ 0.0^″^ to 3° 34′ 30.64^″^.

### Sample size calculation

#### Sample size of study participants

Three wards in Ife North (Ipetu II, Edunabon I and Moro) and two wards in Ife East (Modakeke I and Modakeke II) have been randomly selected to serve as the intervention and control arms respectively. The investigators anticipate the problem of contamination by potential study participants in the control arm who live in wards that share a boundary and are in proximity with the intervention arm. This was mitigated by excluding the wards in the control LGA located at the boundary region between the two LGAs before carrying out the random sampling to select the wards in the two LGAs. Okooko, Edunabon and Moro PHCs which serve Ipetu II (with screening population of about 2926), Edunabon I (with screening population of about 998) and Moro (with screening population of about 1876) wards respectively in Ife North LGA as well as Adeowo and Okebode PHCs which serve Modakeke I (with screening population of about 2251) and Modakeke II (with screening population of about 2249) wards respectively in Ife East LGA have been selected as the 5 PHCs where recruitment of women into the study will take place.

The 3 selected wards in Ife North LGA have an estimated total screening population (women 40–70 years) of 5,800 while the 2 selected wards in Ife East LGA have an estimated total screening population of 4,500. With an anticipated participation rate of about 70% (which is projected from the number of women willing to undergo CBE screening in a previous study in the same state [14]), we project that about 4,100 women will undergo breast evaluation in the intervention arm during the study period. The sample size of 4100 refers to the total number of patients to be accrued broadly in the intervention arm (Ife North LGA). Even though there have been three wards randomly selected in Ife North LGA and two wards randomly selected in Ife East LGA, we will assume that the rate of recruitment of patients will be the same in the randomly selected wards. In each study arm, the CDR is expected to be the same across the wards since they are expected to be similar in terms of health provider density and risk factor profile like genetic makeup, age at first-term pregnancy, parity, and family history of patients presenting for breast evaluation. Because we expect there to be no statistically significant differences in risk factors between the wards within each LGA, we do not incorporate any design effects in sample size calculation.

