#### Sample size of cases

The sample size of 4100 study participants anticipated in the intervention arm (Ife North LGA) will include both asymptomatic (40–70 years) and symptomatic (30–70 years) women that will undergo screening and diagnostic evaluations respectively. In any screening exercise, there will be symptomatic cases that will use the opportunity of screening to present for evaluation. We anticipate a CDR of at least 3.5%. This expectation is supported by our previous publication of a mixed screening and diagnostic population in this geographic region demonstrating a breast CDR of 3.5% [19]. The CDR in this study will be the number of cancers detected among all study participants, including both the symptomatic and screening arms.

Our previous data demonstrate that the mean breast tumor size from an entirely symptomatic population at OAUTHC was 10.5 cm. This is much larger than findings from our recent study from the same region which included a screening population which demonstrated an average breast cancer size of 3.3 cm [19, 22]. We therefore project that cancers in the intervention community will be follow a similar pattern.

The primary outcome measure in this study is the stage at diagnosis. To achieve this, we projected the number of cases needed to detect a difference in the proportion of cases based on stage at diagnosis between the two study arms. From our preliminary data of 25 staged cancers, there were 7 (7/12, 58.3%) and 2 (2/13, 15.38%) stage IV cancers in the control and intervention arms respectively, with a 43% difference between the two groups. In order to detect a 43% difference in stage IV diagnoses between the two study arms with 80% statistical power at an alpha of 0.05, 23 cases will be needed in each arm. Our preliminary data show 13 total cancer cases detected in 791 patients and 12 total cancer cases detected in 82 patients in the intervention and control arms, respectively, in the first year. Going by this annual accrual rate, in two years, there should be 26 cancer cases out of 1582 patients in the intervention arm and 24 cancer cases out of 164 patients in the control arm. Therefore, achieving the 23 cases required for statistical significance in the stage at diagnosis in each arm at the end of the 2-year study period is possible.

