### Statistical analyses

All data entered into the REDCap database will be exported as a dataset into R 4.2. Sociodemographic characteristics of the participants will be assessed using medians and interquartile ranges (IQR) for continuous variables and counts and percentages for categorical variables. Participation rate, retention rate, abnormal call rate, rate of late-stage diagnosis, and CDR will be reported as proportions with 95% exact confidence intervals. As for late-stage diagnosis, stage 4 cancers will be considered late-stage. The above-mentioned metrics will be compared between the intervention and control arms using Chi-square tests or Fisher’s exact test. The time intervals from presentation to treatment will be reported using medians and IQR and will be compared between the intervention and control arms using the Wilcoxon rank-sum test. The rate of late-stage diagnosis will be estimated and compared between the intervention and control arms on a yearly basis, starting from baseline, to assess if the intervention arm shows betterment in this rate consistently. Bonferroni correction for type I error will be implemented (α* = 0.0167) for this comparison. A logistic regression analysis which accounts for the ward (random effect) in which the patient was examined will also be performed with late-stage diagnosis as the dependent variable and time of screening, the interaction between the allocated groups (intervention and control arms), and time of screening as the independent variables. For all statistical comparisons (other than the one mentioned immediately above), the type I error rate (α) will be set to 0.05. All statistical analyses will be conducted using R 4.2 software [24]. Sample size calculations were done using the clinfun package of the R 4.2 software [25].

We do not anticipate any missing data due to loss of follow-up because the research team will make every effort to retain recruited participants. However, if missing data issues do arise, we will implement multiple imputation techniques, which impute missing data under the missing at random (MAR) assumption. Sensitivity analysis of the findings after multiple imputations will thereby be performed and these findings will be compared to those obtained from complete case analyses.

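### The study is labelled randomised, but one LGA per arm confounds programme with place, and the power and p-values hold only for independent cases and LGAs that do not otherwise differ

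*Protocol article*

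**What the plan says.** The Methods paragraph of the abstract and the section Study design and setting both use the randomised label: "The study will use a randomized two group clinical trial design with one LGA serving as the intervention arm", with Ife North as intervention and Ife East as control.

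The section Sample size of study participants says that three wards in Ife North and two in Ife East "have been randomly selected to serve as the intervention and control arms respectively". It describes this step as random sampling of wards in the two LGAs, done after boundary wards in the control LGA had been removed. On clustering it states "we do not incorporate any design effects in sample size calculation". The reason given is that no significant differences in risk factors are expected between wards within an LGA.

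The section Sample size of cases takes its effect from preliminary data ("there were 7 (7/12, 58.3%) and 2 (2/13, 15.38%) stage IV cancers in the control and intervention arms respectively") and concludes that "with 80% statistical power at an alpha of 0.05, 23 cases will be needed in each arm". It projects 26 intervention and 24 control cases over two years.

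Statistical analyses compares the arms with chi-square or Fisher tests. It adds a logistic regression for late-stage diagnosis with ward as a random effect.

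Study design and setting calls the LGAs similar. It also says that the control LGA "has adequate access to screening and diagnostic evaluation because it is about 4 kilometers to the OAUTHC", while the intervention LGA is about 25 km away.

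**The concern.** Random sampling of wards within an LGA makes those wards representative of it. It does not allocate anything to an arm. No random allocation of wards or LGAs to arms is described, and even a chance allocation of two LGAs would leave one unit per arm. Arm and LGA are then the same variable, and the protection that a reader expects from the word randomised is absent.

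The reason for omitting a design effect concerns detection rate and risk factors between wards within an LGA. It does not address clustering of stage at diagnosis, the primary outcome, or differences between the LGAs. Expecting a non-significant difference is also not the same as an ICC of zero.

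The Discussion plans to take the results to the State Commissioner of Health and the national cancer control committee. A difference between two places could be presented there as a randomised programme effect.

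**Working it through.** **Inputs from the article.** Stage IV 7/12 = 58.3% (control) and 2/13 = 15.4% (intervention); alpha 0.05; 80% power; 23 cases per arm; 24 control and 26 intervention cases projected; 2 control and 3 intervention wards. Sidedness is not stated; I take two-sided, because one-sided formulas give 15 (uncorrected) or 19 (continuity-corrected), not 23.

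**1. The plan's own figure.** Exact two-sided Fisher power for 58.3% v 15.4%, by enumeration, is 78.6% at 22 per arm and 81.4% at 23. So 23 is reproduced, for independent cases. At the projected 24 and 26 it is 88%.

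**2. Ward clustering (assumed ICC).** Design effect DE = 1 + (m − 1) × ICC, with m = 24/2 = 12 (control) and 26/3 = 8.67 (intervention). Effective cases = cases/DE, rounded to whole cases for the Fisher calculation. This assumes that every case comes from a selected ward and that wards contribute equally.

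| Ward ICC | DE control / intervention | Effective cases control / intervention | Fisher power |
|---|---|---|---|
| 0 | 1 / 1 | 24 / 26 | 88% |
| 0.01 | 1.11 / 1.08 | 21.6 / 24.1, as 22 / 24 | 83% |
| 0.05 | 1.55 / 1.38 | 15.5 / 18.8, as 15 / 19 | 71% |
| 0.10 | 2.10 / 1.77 | 11.4 / 14.7, as 11 / 15 | 59% |

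Recruiting more from the same wards helps slowly, because ward size grows too. With k wards fixed, n = 23(1 − ICC)/(1 − 23 × ICC/k). At ICC 0.05 this is 21.85/0.6167 = 35.4, so 36 cases, for k = 3, and 21.85/0.425 = 51.4, so 52 cases, for k = 2.

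**3. LGA differences (assumed SD).** I simulated 24 v 26 cases with no programme effect, a common stage IV rate of 40% (the preliminary data pool to 9/25 = 36%), and an independent normal shift on the logit scale for each LGA. Rejection rates at nominal 5%:

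| SD per LGA | Fisher | Chi-square, continuity-corrected | Chi-square, uncorrected |
|---|---|---|---|
| 0.3 | 9% | 8% | 13% |
| 0.5 | 18% | 16% | 23% |

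With no LGA shift, the uncorrected chi-square already rejects at about 6.2% for these sizes, so not all of its excess comes from LGA differences. For scale, the difference between the two LGAs has SD √2 × 0.3 = 0.42 to √2 × 0.5 = 0.71 on the logit scale, or odds ratios of about 1.5 to 2.0 at one SD.

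**4. What the design can estimate.** Between LGAs: 2 − 2 = 0 degrees of freedom, so LGA variation cannot be estimated. Between wards within arms: 5 − 2 = 3. A ward-level t test at 23 per arm and ICC 0 has non-centrality 0.4295/√[(0.2431 + 0.1302)/23] = 3.37 against a critical value of 3.18, giving about 62% power.

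**The case against.** The strongest defence is that the article already plans a model with a ward random effect, that the projected cases exceed 23, and that every shortfall above rests on an ICC or SD that the article does not give. Much of this stands.

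- A reader might infer that the 80% power is simply false. The documents do not support that: at a ward ICC of 0.01, Fisher power is still 83%. The power is conditional on an unstated ICC.
- A reader might infer that the false-positive rate must exceed 5%. That too depends on the size of LGA differences, which is assumed here, and on which test is used.
- A reader might call the ward random effect a contradiction of the omitted design effect. It is an inconsistency: the model is an additional analysis and not the basis of the sample size. It also cannot remove LGA confounding, since its wards are nested in the LGAs.
- A reader might take 25 km versus 4 km as biasing the result towards the programme. On its face, nearness favours earlier diagnosis in the control LGA, so the net direction of bias is unknown.
- Equal ward sizes are a simplification. The intervention wards have screening populations of about 2926, 998 and 1876, and control cases may include women from elsewhere in the LGA who refer themselves to the hospital.

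The phrase about wards being selected to serve as the arms could be read as allocation. But the wards were drawn separately within LGAs whose arms are already fixed.

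**Conclusion.** The point holds in this form. The article describes no random allocation to arms, and with one LGA per arm the programme effect is fully confounded with any LGA difference; this does not depend on an ICC. The 23 cases and the chi-square or Fisher p-values are correct only if cases are independent and the LGAs do not otherwise differ.

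The size of the problem is less certain. Power moves from 88% to between 83% and 59% over ward ICCs of 0.01 to 0.10, and type I error reaches 8% to 23%, depending on the test, over logit SDs of 0.3 to 0.5. Both ranges are assumptions. Neither more cases nor a ward-level correction repairs the comparison, so the claim itself must change.

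**What to change.** 1. In the abstract and in Study design and setting, replace the randomised label with *non-randomised two-community controlled study*, and limit the conclusion to an association between LGAs.
2. Replace the design-effect sentence with a statement that the 80% power assumes independent cases and no LGA difference. Report power over a ward ICC range such as 0.01 to 0.10.
3. Report the chi-square or Fisher result as unadjusted, beside a ward-clustered estimate with a small-cluster correction. State that, with five wards nested in two LGAs, neither removes LGA confounding.
4. Only if existing records at the referral hospital hold stage and LGA, report the pre-launch stage mix by LGA as the baseline to which Statistical analyses refers. The article does not show whether they do.

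Items 1 and 2 cost wording and a short calculation, item 3 one further analysis, and item 4 a record abstraction of unknown feasibility. No redesign is asked for in a study already in its implementation phase. The downside is a less favourable stated power and a weaker causal claim.
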